#### Feasibility, usability, and user acceptance surveys

All participants will be required to complete a technology survey which has been adapted from an earlier survey created by [name]
[47]. It includes questions on ownership of technological devices (i.e., type of computer, games console, tablet, and mobile phone), self-perceived ability to learn how to play digital games, internet use, intergenerational relationships, length of time and frequency of digital game playing, preference of digital game genres, intention to play digital games in the future, purchasing habits of digital games, purpose for buying the digital games, and social activities.

Usability and enjoyment will be assessed in the intervention group using the System Usability Scale (SUS) and the Physical Activity Enjoyment Scale (PACES). The PACES
[48,49] will assess enjoyment of the exercises, and the SUS
[50] will assess the usability of the iStoppFalls system.

The Activity Flow State Scale (AFSS) created by Payne et al.
[51] was adapted from an earlier scale called the Flow State Scale (FSS) created by Jackson and Marsh
[52]. The AFSS comprises of 26 items which are measured on a 5-point Likert scale ranging from 1 (strongly disagree) to 5 (strongly agree).

The AttrakDiff2 questionnaire initially created and further developed by Hassenzahl et al.
[53,54] will be used to examine the usability of the exergames by addressing hedonic and pragmatic qualities, attractiveness, as well as identification with and stimulation through the iStoppFalls program. The questionnaire comprises 28 items which are measured on a 7-point Likert scale.

The Technology Acceptance Model (TAM)
[55] is applied to measure the user acceptance of a system or technology. In its original form the TAM provides two dimensions of technology acceptance ‘perceived benefit’ and ‘perceived ease of use’. In this study an extended version as suggested by F. Davis
[56] was used, including the dimensions ‘perceived effort’ and ‘perceived design’. Constructs of the Unified Theory of Acceptance and Use of Technology Model (UTAUT), as well as computer self-efficacy and trust will be added to the original TAM. The analyses will show the validity of this acceptance model in regard to the user acceptance of iStoppFalls.

#### Mid-term assessments

After eight weeks, participants will be sent the following questionnaires by mail: Icon-FES, IPEQ or PAQ-50+, and EQ-5D-5-L. For the intervention group, the sensor-based physical assessments will be repeated at the participants’ homes.

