### Randomization and blinding

Following successful baseline assessments, participants will receive a unique computer-generated random number for identification (ID). A research assistant will then allocate the participants’ ID to the intervention or control group (ratio 1:1) by using permuted block-randomisation (software available from
https://apps.neura.edu.au/blinders/). Couples (participants living in the same household) will be treated as one unit and randomised into the same block. Reassessment will be performed by experienced and trained research assistants (RA) who are blinded to group allocation. To avoid unblinding of the RA, participants will be reminded not to talk about their user experience during the reassessments.

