[13]. If the calendars are not returned, filled out incorrectly, or show non-adherence, participants will be contact by phone by a blinded (falls) and unblinded (adherence) RA, respectively. Participants will receive individual training reminders in the middle and the end of each week via the iStoppFalls system. Additionally, participants will be reminded by an unblinded RA to perform at least one interactive fall risk assessment (including questions about fall history and self-administered physical tests of balance, reaction time, and strength) each month.

Participants will be required to give written informed consent prior to inclusion. Ethical approval was obtained by the ethics committees of the German Sport University Cologne (24.09.2013), the Polytechnic University of Valencia (19.12.2013), and the Human Research Ethics Committee of the University of New South Wales (reference number HC12316, 19.12.2013). This trial will be conducted according to the ethical standards of the Helsinki Declaration.

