#### Outcome measures

Participants will be assessed at baseline (0 weeks), in the middle (8 weeks), and at the end of the intervention period (16 weeks). The assessments will be conducted under standardized conditions at the study centres or in rooms provided by the retirement villages. Table 
1 outlines the assessments performed at different time points. Each assessment will take about two hours to complete. When a stopwatch is used, time will be recorded to the nearest 0.01 s. For the Timed Up and Go (TUG), walking, and sensor-based assessments, participants will be wearing a SMM device as a necklace at the height of the sternum.

**Table 1 T1:** Study assessments by time point

**Type of assessment**		**Outcome variable**	**Baseline assessments (week 0)**	**Re-assessments (week 8)**	**Post-assessments (week 16)**
Health	Demographics, health status, falls history	NA	X		
	12-item WHODAS 2.0	Secondary	X		X
	European Quality of Life – 5 Dimensions	Primary	X	X	X
	Iconographical – Falls Efficacy Scale	Secondary	X	X	X
	Falls and exercise adherence calendars	Secondary		Monthly	
Technical	Technology use	Secondary	X		
	SUS & PACES	Secondary		X	
	TAM & UTAUT	Secondary			X
	AttrakDiff2 & AFSS & DART	Secondary			X
Physical	Physiological Profile Assessment	Primary	X		X
	Short Physical Performance Battery	Secondary	X		X
	Sensor-based balance tests	Secondary	X	X	X
	Sensor-based reaction time tests	Secondary	X	X	X
	Sensor-based chair stand test	Secondary	X	X	X
	Timed Up and Go test	Secondary	X		X
	Steady-state walking speed (single and dual task)	Secondary	X		X
	Hand grip strength	Secondary	X		X
	IPEQ or PAQ-50+	Secondary	X	X	X
Cognition	Mini-Cog	NA	X		
	Addenbrooke’s Cognitive Examination III	Secondary	X		X
	Trail Making Test	Secondary	X		X
	Victoria Stroop test	Secondary	X		X
	Digit Symbol Coding test	Secondary	X		X
	Digit Span Backward	Secondary	X		X
	Attention Network Test	Secondary	X		X
	Counting backwards by three	Secondary	X		X
iStoppFalls system	Exercise adherence	Secondary		Continuously	
	User activity (i.e., set top box, tablet)	Secondary		Continuously	
Kinect sensor	Range of motion	Secondary	While exercising		
	21 Joint angles	Secondary	While exercising		
SMM sensor	Walking distance (m)	Secondary		Daily	
	Peak power sit-to-stand transfers (W)	Secondary		Daily	

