#### Sensor-based physical assessments

Four sensor-based physical assessments using the iStoppFalls software, the Microsoft Kinect, and the SMM will be performed barefoot in front of a TV: (1) Balance tests include comfortable-bipedal, semi-tandem, near-tandem, and tandem stance (Figure 
5). Each balance task will be repeated twice for a maximum duration of 30 s with the preferred foot in front (no changes allowed between the different stances) and eyes open. After the countdown ‘ready, set, go’, time will be stopped when the participant moves his/her feet, touches the chair for support, or successfully reaches 30 s. (2) The hand reaction time test will require participants to use their hands to hit two randomly flashing lights positioned to the left and right on a virtual table. Two sets of 20 repetitions will be performed. (3) For the stepping reaction time test, two randomly flashing lights will be positioned to the left and right on a virtual floor. Participants will need to perform a lateral step onto the flashing light as fast as possible. Stepping should include weight-shifting rather than only foot tapping to the side. Two sets of 20 repetitions will be performed. (4) The sit-to-stand test is a functional measure for lower extremity strength, power, and balance. Participants will be instructed to cross their arms over the abdomen, and rise from a chair for five times as quickly as possible. Time measured by a stop watch indicates insufficient (≥16.7 s), sufficient (13.7 s to 16.6 s), good (11.2 s to 13.6 s), and very good strength performance (≤11.1 s)
[38].

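### Only the intervention arm practises on the system that delivers the sensor-based tests, so their week-16 group comparison mixes familiarity with physical change; who runs the one-arm week-8 home test is also left open

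*Protocol article*

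**What the plan says.** All references are to the protocol article.

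- **Status of the tests.** Table 1 (Outcome measures) lists the sensor-based balance, reaction-time and chair-stand tests as secondary, at weeks 0, 8 and 16: "Sensor-based balance tests Secondary X X X". The rows carry no group restriction.
- **Equipment.** Under Sensor-based physical assessments: "Four sensor-based physical assessments using the iStoppFalls software, the Microsoft Kinect, and the SMM will be performed barefoot". The section on the iStoppFalls system says one application serves both the exercises and the fall risk assessments.
- **Who has the system.** Study design gives the equipment to the intervention group after randomization. Controls keep their habitual exercise routine.
- **Monthly self-tests.** Study design has an unblinded research assistant remind participants to complete at least one fall risk assessment on the system, including "self-administered physical tests of balance, reaction time, and strength) each month".
- **Week 8.** Under Mid-term assessments: "For the intervention group, the sensor-based physical assessments will be repeated", in their own homes. The week-8 questionnaires are posted, with no group limit.
- **Analysis.** Statistical analyses and sample size plans a baseline-adjusted ANCOVA for the intervention effect on outcome measures at follow-up and excludes no outcome. It also plans paired t-tests and repeated measures ANOVA within groups.
- **Blinding.** Under Randomization and blinding: "Reassessment will be performed by experienced and trained research assistants (RA) who are blinded to group allocation". No visit is excepted.

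**The concern.** A between-group comparison at week 16 is interpretable as a physical effect only if the measurement works the same way in both arms. Here one arm spends 16 weeks on the device that administers the test and repeats similar tests on it, while the other meets it only at the assessments. Someone who has learned how the sensor responds, or how to react to a target on a screen, can score better without being steadier, faster or stronger. Such a gain could be reported as an effect on balance, reaction time or strength.

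The second issue is smaller. At week 8 only one arm has the home sensor test, so anyone who conducts it knows the allocation. The blinding statement does not allow for this.

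**Working it through.** **1. Exposure between baseline and week 16**

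| | Intervention | Control |
|---|---|---|
| System at home | yes | no |
| Recommended balance exergames | 120 min/week × 16 = 32 h | none |
| Recommended strength training on the system | 45 to 60 min/week × 16 = 12 to 16 h | none |
| Self-tests on the system | at least one a month, so about 4 | none |
| Week-8 sensor test | one, at home | none |

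The total is 44 to 48 h; Design of intervention rounds this to about 50 h. These are recommended minimum amounts, neither a ceiling nor a forecast of actual use. The self-tests cover the same domains as the outcome tests, but the protocol does not say that they are identical.

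**2. Where familiarity should matter most**

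- Hand and stepping reaction tests: the participant responds to flashing targets on a virtual table or floor. One exergame trains side-stepping to collect objects, close to the lateral step that the stepping test scores. This is the clearest overlap.
- Balance stances: scored by holding time up to 30 s. Device familiarity matters less here, though the stance can be rehearsed.
- Chair stand: timed by stopwatch. Device familiarity matters least.

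**3. Why baseline adjustment does not help**

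Let the expected week-16 score in the intervention arm be shifted by τ + π, where τ is the physical effect and π is the net gain from extra practice. At baseline neither arm has used the system at home, so the baseline score carries no information on π. The ANCOVA group coefficient therefore estimates τ + π. The within-arm change also contains π, so moving to a within-arm analysis does not remove it. It only avoids presenting it as a randomized effect.

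**4. The plan's own figure**

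The protocol gives no figure for practice. Its sample size serves to check the power formula: ANCOVA with λ = f²N, df = 1 and N − 3, α = 5%. With f = 0.40 and N = 52, λ = 0.16 × 52 = 8.32 and power is 0.807. At N = 51 it is 0.799. So 52 is the smallest N that reaches 80%, as stated. It is based on the PPA, which is not taken on the system.

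**5. Illustration of the size (π is assumed, not from the protocol)**

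Set τ = 0 and π = d SD. Take N = 160 × 0.85 = 136, applying the 15% dropout given for two sites to the whole trial. With baseline correlation r, f = (d/2)/√(1 − r²). Example: d = 0.3 and r = 0.5 give f = 0.15/√0.75 = 0.173, λ = 0.03 × 136 = 4.08 and a rejection rate of 51.8%.

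| Assumed practice gain | r = 0 | r = 0.5 |
|---|---|---|
| 0.1 SD | 8.9% | 10.3% |
| 0.2 SD | 21.2% | 26.7% |
| 0.3 SD | 41.2% | 51.8% |
| 0.5 SD | 82.5% | 91.7% |

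The nominal rate is 5%. Higher correlation makes the test more sensitive to the practice gain.

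**6. Blinding at week 8**

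The blinding statement covers reassessment without exception, and Table 1 heads the week-8 column as re-assessments. Mid-term assessments gives the sensor tests to one arm, in the home where the system is installed. If staff conduct that test, they cannot be blinded. The article does not say who conducts it. Study design already separates blinded from unblinded assistants for telephone contact, so unblinded staff exist.

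**The case against.** **No between-group claim is stated for the sensor tests.** Table 1 also labels intervention-only measures, such as the usability and enjoyment scales, as secondary, and the planned within-group analyses suit three time points in one arm. This has force. But the sensor tests are marked at baseline and week 16 with no restriction in the text, unlike the week-8 home test. The ANCOVA sentence excludes nothing, and the sample size is said to suffice for between-group differences in continuous physical measures. The comparison is open to be made.

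**Table 1 is not in error.** It leaves other intervention-only measures unmarked too. This stands: marking the week-8 sensor rows is a clarification.

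**Practice will not affect all sensor tests equally.** This stands, and the point is graded accordingly.

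**Blinding of the primary outcome.** A reader might infer that assessor blinding of the week-16 PPA is lost. The article does not support that. It would need the same staff at both visits, which is neither stated nor ruled out, or allocation revealed by a participant's visible ease with the system, which is not described. Unblinded staff or self-administration at week 8 are both possible, and rostering is a detail that an article may leave to the full protocol. What remains is a blinding statement too broad for a one-arm visit.

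**Conclusion.** The point holds for the sensor-based secondary outcomes. Their week-16 baseline-adjusted comparison would confound physical improvement with test and device familiarity. The confounding is strongest for the hand and stepping reaction tests and weakest for the stopwatch-timed chair stand. The expected direction favours the intervention. The size is unknown: the error rates in the working depend on an assumed practice gain and show only that even a modest gain would matter. The conclusion rests on the system being in intervention homes only and on the monthly assessment being delivered through it, which the article supports.

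The primary outcomes (PPA and EQ-5D) are not taken on the system, and the sample size is unaffected. On blinding, the finding is a mismatch in wording at week 8. It becomes a risk at week 16 only if the same staff assess then. This is a worthwhile, inexpensive improvement and does not threaten the main result.

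**What to change.** 1. Declare the sensor-based outcomes within-arm or exploratory, and state that practice on the system is confounded with physical change, within the arm as well as between arms.
2. Base between-group claims on physical effectiveness on tests not taken on the system: the PPA first, then the Timed Up and Go, which is timed by stopwatch although the motion sensor is worn. Note that the SPPB shares semi-tandem and tandem stances and five chair stands with the sensor tests, so it is not free of task practice.
3. Limit the blinding statement to the week-16 assessments. Assign the week-8 home tests to unblinded staff and bar them from assessing at week 16.
4. Mark the week-8 sensor rows of Table 1 as intervention-only. The week-8 questionnaires stay unrestricted.

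The cost is wording and rostering of staff the trial already has. The real loss is that the sensor tests no longer support an effectiveness claim.

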#### Statistical analyses and sample size

A priori power analysis has been conducted for PPA as the primary outcome by using data from a previous study. The estimated sample size of 52 participants for the individual study sites in Cologne and Sydney is based on a large effect (f = 0.40) for the PPA (ANCOVA, alpha 5%, power 80%, numerator df 1, number of groups 2, number of covariates 1)
[57]. With an anticipated dropout of 15%, 60 participants will be recruited. The sample size will be sufficient for determining clinically significant between-group and within-group differences as well as main interaction effects in the continuously-scaled physical and cognitive outcome measures. For this study the intention-to-treat method will be used. Data on feasibility will be analysed using descriptive techniques. Student t-tests (for continuous variables with normal distribution), Fisher's exact test (for nominal data, small sample size), and Mann–Whitney U test (for ordinal or continuous data without normal distribution) will be used to determine differences between the intervention and control group at baseline. Analysis of covariates (ANCOVA) will be used to determine the intervention effect on outcome measures at follow-up adjusting for baseline values. Negative binomial regression will be used to test for differences in fall rates between groups. Paired t-tests and repeated measures ANOVA will be used to analyse changes within groups and to explore subgroups (e.g., different doses) in the intervention group. The alpha level will be set at 5%. Analyses will be performed with SPSS version 23 for Windows (SPSS, Inc., Chicago, IL). Reporting of the trial will follow CONSORT
[58] statement for non-pharmacological interventions and the SPIRIT
[59] guidance for protocols of clinical trials.

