## Abstract

**Background:**

Falls are very common, especially in adults aged 65 years and older. Within the current international European Commission’s Seventh Framework Program (FP7) project ‘iStoppFalls’ an Information and Communication Technology (ICT) based system has been developed to regularly assess a person’s risk of falling in their own home and to deliver an individual and tailored home-based exercise and education program for fall prevention. The primary aims of iStoppFalls are to assess the feasibility and acceptability of the intervention program, and its effectiveness to improve balance, muscle strength and quality of life in older people.

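### The article names PPA as the single primary outcome in its power calculation but labels both PPA and EQ-5D primary in Table 1, with no rule linking the two tests

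*Protocol article*

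**What the plan says.** Three places in the protocol article bear on which outcome is primary.

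- **Statistical analyses and sample size.** One primary outcome: "A priori power analysis has been conducted for PPA as the primary outcome by using data from a previous study". The calculation is specified as "ANCOVA, alpha 5%, power 80%, numerator df 1, number of groups 2, number of covariates 1", with f = 0.40 for PPA. It gives 52 participants for each of Cologne and Sydney, raised to 60 for 15% dropout. The section later adds "The alpha level will be set at 5" per cent, and applies ANCOVA with baseline adjustment to outcome measures generally.
- **Outcome measures, Table 1.** Two primary outcomes. The EQ-5D row reads "European Quality of Life – 5 Dimensions Primary X X X" (weeks 0, 8 and 16). The PPA row begins "Physiological Profile Assessment Primary X" and is marked for weeks 0 and 16 only.
- **Abstract, Background.** "The primary aims of iStoppFalls are to assess the feasibility and acceptability of the intervention program", together with "its effectiveness to improve balance, muscle strength and quality of life in older people".

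The section on demographic and general health describes two quantities from EQ-5D: a health index built on five dimensions and a separate 0 to 100 rating. Table 1 does not say which of them is primary.

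**The concern.** The primary outcome determines what the trial may claim. Here the power section has one and Table 1 has two. The second does not look like a typing slip, because quality of life also stands among the primary aims in the abstract.

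The two outcomes are not on an equal footing. PPA has an effect size, an alpha and a power. EQ-5D has none of these, and the general statement that the sample is sufficient refers to continuous physical and cognitive measures, which leaves quality of life out. EQ-5D is also completed by participants who know whether the system was installed in their home, since the blinding described is that of the reassessment staff.

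With one 5% level and no rule connecting the two tests, the choice of deciding outcome could be made after the results are seen. A positive finding on either could then be presented as the primary result.

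**Working it through.** **Inputs.** From the statistics section: alpha 0.05, power 0.80, f = 0.40, numerator df 1, two groups, one covariate, 52 per site, 15% dropout. From the participants section: 160 recruited in all. The article gives no correlation between the PPA and EQ-5D test statistics, so a range is assumed.

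**1. The plan's own figure.** ANCOVA power from the noncentral F distribution with λ = f²N, df1 = 1 and df2 = N − 2 − 1.

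- N = 52: λ = 0.16 × 52 = 8.32, df2 = 49, power = 80.7%.
- N = 51: power = 79.9%.

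So 52 is the smallest N that reaches 80%, exactly as stated. The 60 recruited corresponds to 52 × 1.15 = 59.8. The sample size is right for PPA as the only primary outcome.

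**2. Familywise error if success on either outcome counts.** Independent tests, each at 5%: 1 − 0.95² = 0.0975, which is 1.95 times 5%. For correlated tests, 1 − P(|Z1| < 1.96, |Z2| < 1.96) under a bivariate normal:

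| Assumed correlation | Familywise error |
|---|---|
| 0 | 9.75% |
| 0.3 | 9.5% |
| 0.5 | 9.1% |
| 0.9 | 7.0% |

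**3. Other success rules.** If PPA alone is primary, the error for the primary claim is 5%. If both must be significant, the chance of wrongly claiming joint success is at most 5%. Neither rule inflates the error.

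**4. Fixed sequence, PPA then EQ-5D, each at 5%.** If PPA has no true effect, any false claim requires a false rejection of PPA first, which has probability 5%. If PPA has a true effect, the only possible false claim is on EQ-5D, again at most 5%. The error for the pair stays at 5%, and PPA keeps its full alpha and its 80.7% per-site power at N = 52.

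**5. Split alpha, 0.025 each.** Error 1 − 0.975² = 4.94% if independent. Consequences for PPA at f = 0.40:

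- Per site, N = 52: power falls from 80.7% to 71.5%.
- Restoring 80% needs N = 63 per site (64 for equal arms). Allowing for 15% dropout, 63/0.85 = 74.1, so 75; 64/0.85 = 75.3, so 76.
- Three sites pooled, 160 × 0.85 = 136 completers: power 99.6% at alpha 0.05 and 99.1% at 0.025, using the same one-covariate formula.

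The power for EQ-5D cannot be computed under any of these rules, because no effect size is given.

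**The case against.** The best defence is that the article does settle the matter: the statistics section speaks of PPA in the singular and powers it alone, and on that reading no error is inflated. A journal article may also leave alpha allocation, testing order and the choice of EQ-5D variable to a fuller document. The second part stands to this extent: silence on multiplicity would not by itself be a finding. But the conflict over how many primary outcomes there are is in the printed text, and an unseen document does not remove it.

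Several stronger readings are tempting and should not be adopted.

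- A reader might infer that the false-positive rate is in fact nearly doubled. That needs an either-outcome success rule and tests that are close to independent. The article states neither.
- A reader might count up to four EQ-5D tests, from two variables at two visits. No section makes week 8 a primary time point: it is described as mid-term, the final reassessment is at 16 weeks, and ANCOVA is at follow-up.
- A reader might quote 1 − 0.95³ = 14.3% for PPA plus two EQ-5D variables. That treats the index and the 0 to 100 rating from one respondent as independent. At an assumed correlation of 0.5 to 0.7 between them, with PPA independent, it is 13.6% to 12.9%, and the either-outcome rule is still an assumption.
- A reader might take 71.5% as the trial's power under split alpha. It applies to one site; the pooled figure is about 99%.
- A reader might count feasibility as a further untested primary claim. The statistics section already says that feasibility data are analysed descriptively, so it adds no hypothesis test.

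**Conclusion.** The inconsistency is certain: one primary outcome in the statistics section, two in Table 1, with quality of life among the primary aims. No rule states how the two tests share the 5%, and EQ-5D has no power basis.

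The effect on error is conditional. Familywise error lies between 7.0% and 9.75% for assumed correlations from 0.9 down to 0 if success on either outcome counts, and does not exceed 5% if PPA alone is primary or both must succeed. Because the article does not say which rule applies, the error for the primary claim is not fixed by the plan. The sample size of 52 per site is not at fault. The point should be resolved before any outcome is analysed.

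**What to change.** Reconcile the abstract's aims, Table 1 and the statistics section as follows.

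- State PPA at week 16 as the primary outcome, the one on which the trial is powered.
- Relabel EQ-5D in Table 1 as key secondary, or as second in a fixed sequence. Name one EQ-5D variable at week 16, tested at 5% only if PPA is significant. If the health index is chosen, settle the instrument version too: the article names the five-level form but describes three levels.
- Align the wording of the aims, so that quality of life has the same rank there as in Table 1. For feasibility, the existing descriptive statement is enough once the aims agree with it.

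The cost is a table label, a few sentences and a change to the abstract. No participants are added and PPA loses no power. The downside is that an effect on EQ-5D cannot be claimed if PPA fails.

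Keeping both outcomes primary is also open to the sponsor. The article should then state the success rule and alpha allocation, give a power basis for EQ-5D, and restate the PPA power. With 0.025 each, that is 71.5% per site at N = 52, or about 99% if the three sites are pooled with 136 completers.

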#### Demographic and general health

Participants will be sent a self-report questionnaire by post and will be requested to complete it prior to the baseline assessment. We will collect information on socio-demographic characteristics (age, gender, marital status, ethnicity, housing situation, economic status, previous occupation, education) and medical history (presence of medical conditions, medication use, history of falls). In addition, the following outcome measures will be assessed at baseline and 16 weeks follow-up.

The 12-item World Health Organization Disability Assessment Schedule (WHODAS) 2.0 is a generic assessment instrument for six domains of general health: understanding and communicating, mobility, self-care, interpersonal interactions, household and work activities, and participation in society (
http://www.who.int/classifications/icf/whodasii/en/). This self-administered questionnaire is short, simple, and easy to administer. It produces standardized disability levels and profiles linked to the International Classification of Functioning, Disability and Health (ICF)
[22].

The Patient Health Questionnaire (PHQ-9) is a 9-item questionnaire for screening, diagnosing, monitoring, and measuring the severity of depression
[23]. Each item is scored from 0 (not at all) to 3 (nearly every day) leading to the diagnosis of minimal (0 to 4 points), mild (5 to 9 points), moderate (10 to 14 points), moderately severe (15 to 19 points), and severe (20 to 27 points) depression. The PHQ-9 showed excellent internal reliability (Cronbach’s alpha = 0.86) and discriminant validity (area under the curve = 0.95)
[23].

The European Quality of Life – 5 Dimensions (EQ-5D-5-L) questionnaire was developed to generate a basic health index (
http://www.euroqol.org/eq-5d-products/eq-5d-5l.html). Participants will describe their health status in five dimensions: mobility, self-care, usual activities, pain/discomfort, and anxiety/depression. Each dimension has three possible levels: (i) no problem, (ii) moderate problems, or (iii) extreme problems. Thus, 243 health states represented by a 5-digit combination can be defined according to the relevant level within each dimension (e.g., 11111 represents no problems on any dimension). In addition, participants will report their overall health during the past 30 days on a continuous scale (0 to 100, higher score equals better health perception)
[24].

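### EQ-5D, Icon-FES and the activity questionnaires are collected in both arms at weeks 8 and 16, but the only stated between-group analysis is a single-visit ANCOVA, which leaves out the week-8 value of anyone who misses week 16

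*Protocol article*

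**What the plan says.** - **Label and visits.** Table 1 under Outcome measures has the row "European Quality of Life – 5 Dimensions Primary X X X", that is weeks 0, 8 and 16. PPA reads "Physiological Profile Assessment Primary X X", the two marks being baseline and week 16. Icon-FES and IPEQ or PAQ-50+ are secondary and also have all three visits.
- **Who supplies week 8.** Mid-term assessments says: "After eight weeks, participants will be sent the following questionnaires by mail: Icon-FES, IPEQ or PAQ-50+, and EQ-5D-5-L". No arm is excluded. The restriction to one arm comes in the next sentence and concerns other measurements: "For the intervention group, the sensor-based physical assessments will be repeated at the participants’ homes".
- **A differing description.** Demographic and general health, which introduces EQ-5D and Icon-FES, says that "the following outcome measures will be assessed at baseline and 16 weeks follow-up" and does not mention week 8.
- **Between-group method.** Statistical analyses and sample size says: "Analysis of covariates (ANCOVA) will be used to determine the intervention effect on outcome measures at follow-up adjusting for baseline values". No week is given in that sentence.
- **Repeated measures.** The same section assigns paired t-tests and repeated-measures ANOVA to changes within groups and to subgroups of the intervention arm.
- **Analysis principle and loss.** "For this study the intention-to-treat method will be used". The anticipated dropout is 15%.

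**The concern.** A baseline-adjusted ANCOVA has one response per person. Run at week 16, it takes no information from a participant who returned the week-8 questionnaire and then left, unless a further step that the article does not describe is added. Yet that questionnaire is the most recent information on how the person was doing before leaving. Only the intervention arm carries the home exercise programme, so the reasons for leaving could differ between arms. If they do, and if they are related to the week-8 score, the week-16 completers in the two arms are no longer comparable after adjustment for baseline alone. For an outcome labelled primary under a declared intention-to-treat analysis, the stated method then uses less of the collected data than it could, at some cost in precision and possibly in bias.

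**Working it through.** **1. The plan's own figure.** The only calculation in the article is for PPA: ANCOVA with f = 0.40, alpha 5%, power 80%, two groups, one covariate. With noncentrality f²N and N − 3 denominator degrees of freedom, N = 52 gives 0.16 × 52 = 8.32 and power 80.7%; N = 51 gives 79.9%. So 52 is reproduced. The stated 60 is 52 × 1.15 = 59.8, rounded up (dividing by 0.85 gives 61.2). PPA has no week-8 value, so nothing below touches this figure.

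**2. Inputs for EQ-5D.** From the article: 160 participants, 1:1 allocation, 15% dropout. Assumed: that the 15%, stated for the Cologne and Sydney samples, applies to the pooled trial; that all loss occurs after week 8; and the correlations between visits. The article gives no EQ-5D standard deviation, correlation or week-8 return rate. This gives n = 136 completers and up to m = 24 dropouts with a week-8 value.

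**3. Precision, if loss is random.** The variance of the week-16 mean using the dropouts' week-8 values, relative to completers only, is 1 − r² × m/(n + m), where r is the week-8/week-16 correlation given baseline.

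| r | all 24 returned week 8 | 12 returned week 8 |
|---|---|---|
| 0.3 | 1 − 0.09 × 24/160 = 0.987 | 1 − 0.09 × 12/148 = 0.993 |
| 0.5 | 1 − 0.25 × 24/160 = 0.963 | 1 − 0.25 × 12/148 = 0.980 |
| 0.7 | 1 − 0.49 × 24/160 = 0.927 | 1 − 0.49 × 12/148 = 0.960 |

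To place r: raw correlations of 0.7 (baseline with week 8), 0.6 (baseline with week 16) and 0.7 (week 8 with week 16) give r = (0.7 − 0.7 × 0.6)/√((1 − 0.49)(1 − 0.36)) = 0.28/0.571 = 0.49. All correlations at 0.6 give r = 0.24/0.64 = 0.375. So about 1 to 4% is the realistic range, and the 7% corner needs a partial correlation of 0.7 with every week-8 form returned. In power, at f = 0.24 with 136 completers, 79.4% rises to between 79.5% and 82.3% over the grid r = 0.3 to 0.7 with 25 to 100% of dropouts returning week 8.

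**4. Bias, if loss is not random.** Simulations used 80 per arm and 4,000 trials per scenario. The two-visit estimate predicts the missing week-16 value from baseline, group and week 8, which is in effect what the mixed model does.

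All correlations 0.6, true effect 0.30 SD, 12 to 15% missing:

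| Dropout depends on week-8 score | ANCOVA, completers | using week 8 |
|---|---|---|
| not at all | 0.296 | 0.296 |
| equally in both arms | 0.291 | 0.297 |
| in the intervention arm only | 0.326 | 0.298 |
| in opposite directions | 0.362 | 0.299 |

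The simulation error of each mean is about 0.137/√4000 = 0.002.

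Correlations 0.7/0.6/0.7, poor week-8 scorers more likely to leave:
- intervention arm only, 15% loss: ANCOVA bias +0.04 to +0.06 SD; at 20% loss, about +0.07 SD;
- control arm only, 15% loss: −0.03 to −0.04 SD;
- same dependence in both arms, or random loss: about 0;
- intervention arm only, with half the dropouts returning week 8: the two-visit estimate keeps a bias of 0.01 to 0.02 SD.

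The standard error of the group difference is 0.137 SD, so a bias of 0.04 is 0.04/0.137 = 0.29 standard errors and one of 0.07 is 0.51.

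**The case against.** Much of the case on the other side stands.

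- *The time point is not really open.* The Abstract places the final reassessment at 16 weeks, Demographic and general health uses the word follow-up with 16 weeks, the week-8 section is headed as mid-term, and Table 1 calls week 16 the post-assessment. A reader might infer from the ANCOVA sentence alone that the time point is unspecified; the article as a whole points to week 16.
- *No second EQ-5D test is stated.* A reader might infer two unranked between-group tests, one per visit, and from that a false-positive rate of 8 to 10%. No sentence sets out two such tests, so that figure is not supported and is not part of this point.
- *No complete-case rule is stated.* A reader might infer that the plan orders week-8 data to be thrown away. It does not; it declares intention to treat, and a missing-data rule may sit in an analysis plan that is not shown. What stands is narrower: the article does name its between-group method, and that method has no place for the week-8 value.
- *The bias scenario is chosen.* It needs dropout that depends on the week-8 score differently by arm. Nothing in the article shows this, and the direction could go either way. Under Design of intervention, participants who stop exercising may still attend reassessment, so stopping the programme need not mean a missing week 16.
- *Single-visit ANCOVA is valid and standard.* True; the mixed model is an improvement on it, not the repair of an error.

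**Conclusion.** The point holds as a modest, nearly free improvement to a stated method. For three outcomes with two follow-ups in both arms, one of them labelled primary, the stated comparison uses only one follow-up. Using both would reduce the variance by about 1 to 4% and protect against a bias of roughly 0.03 to 0.07 SD. That bias can favour either arm, arises only if dropout depends on the week-8 score differently by arm, and is only partly removed if some dropouts did not return week 8. These sizes rest on 80 per arm in a pooled analysis, 15 to 20% loss after week 8 and assumed correlations; none of the EQ-5D inputs is in the article. PPA, on which the trial is powered, is not affected. A reader should not go further and conclude that the EQ-5D result would be invalid, that it would be biased towards the programme, or that its type I error is inflated by multiple visits; the article does not support any of these. Separately, the description of assessment times in Demographic and general health does not match Table 1 and Mid-term assessments, and should be aligned.

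**What to change.** 1. For EQ-5D, Icon-FES and IPEQ or PAQ-50+, replace the single-visit ANCOVA with a mixed model for repeated measures. The responses are the week-8 and week-16 values; the terms are group, visit, group-by-visit, baseline and baseline-by-visit; the covariance is unstructured; and everyone with at least one follow-up is included. The baseline-by-visit term is needed because baseline may predict the two visits with different strength. IPEQ and PAQ-50+ are on different scales (hours per week and energy expenditure), so each needs its own model.
2. Name the week-16 group contrast as the EQ-5D test, with week 8 supportive.
3. Align Demographic and general health with Table 1 and Mid-term assessments on the week-8 EQ-5D and Icon-FES.
4. Keep baseline-adjusted ANCOVA for PPA and every other outcome with one follow-up in both arms.

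The cost is a sentence or two and a slightly more complex standard model. No new data are needed and the sample size is unchanged. With complete data the week-16 estimate is essentially the ANCOVA estimate.
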